**6. Study Design**

**Phase***

Not applicable

*6.1. Design*

This is a randomized clinical trial comparing two methods of training mental health providers in Prolonged Exposure (PE) treatment for Posttraumatic Stress Disorder (PTSD). Two hundred (200) mental health providers at three medium-to-large CONUS Army installations will be randomly assigned to either Standard PE training or Extended PE training. All providers will receive a 4-day PE workshop, along with the distribution of training materials and treatment manuals, conducted at the military site by the Overall Study PI, [name], and her team. Following the 4-day workshop, participants randomized to the Extended PE training will receive weekly phone consultation with a PE expert on two PE therapy clinical cases followed by twice monthly telephone consultation as needed for six months. Participants randomized to the Standard PE training group will not receive any additional consultation following the workshop. Providers will not be required to use PE therapy to treat their patients with PTSD; using PE will be optional. A major outcome of this study is the proportion of the providers PTSD patients that are offered PE. The mental health outcomes of providers PTSD patients will also be monitored as a second major outcome. Patients seeking care for PTSD from participating providers will be recruited, consented and offered treatment for PTSD and related problems to prospectively and systematically assess what type of treatment they are offered and their response to treatment.

*6.2. Study duration*

The study is expected to start in May 2014 and end in May 2017. Subject recruitment and data collection will mostly occur in years 2, 3, and 4. Data analysis will occur in year 4.

*6.3. Resources necessary for human research protection*

Describe research staff and justify that the staff are adequate in number and qualifications to conduct the research. Describe how you will ensure that all staff assisting with the research are adequately informed about the protocol and their research related duties. Describe access to a population that would allow recruitment of the targeted number of subjects. If medical or psychological services as a consequence of the research, describe how the subject will be referred to those services. Describe your facilities and justify that the facilities are adequate. Verify that there is sufficient time to conduct and complete the research.

*6.4. Research Staff*

Other Technical Staff, to include a Study Coordinator, BOA, and Research Assistant, will be hired by The Geneva Foundation. Their names, biographical information, and documentation of CITI training will be submitted to the IRB for review and approval prior to any interaction with study participants. Ensuring that all staff assisting with the research are adequately informed about the protocol and their research related duties. The Penn investigators will hold regular teleconferences with the performance sites to monitor study progress, identify any adverse events and protocol deviations, communicate any changes or modifications to the study protocol, and problem solve with the site staff. Additionally, Penn investigators will make annual visits to the performance sites to conduct training and provide on-site consultation and monitoring. Access to the Military Sites. In conjunction with her military funders, [name] and her team have made site visits to each of the military performance sites and secured their support for the conduct of this study.

*6.5. Penn Facilities*

Facilities at the Center for the Treatment and Study of Anxiety include 15 offices where patients are seen, all of which are equipped with digital video recorders, printers and computers. Also available are additional offices used for research related activities, including a laboratory equipped for medical screening and taking blood, conference rooms for group supervision, and double locked storage areas for securing confidential records and session tapes.

*6.6 Time to Conduct and Complete the Research.*

This project has funding for four years to conduct and complete the research according to the study timeline and milestone description (see Procedures section).

**7. Characteristics of the Study Population**

*7.1. Target population*

The primary group of participants will include male and female mental health providers regardless of racial or ethnic origin whose job duties include providing psychotherapy to service members with PTSD, and who can be reasonably certain that they will remain at the Army base for at least one year. The secondary group of participants will include male and female military beneficiaries regardless of racial and ethnic origin who are seeking treatment from the participating providers who exhibit clinically significant PTSD symptoms (defined as a severity score of 25 or greater on the Clinician-Administered PTSD Scale for DSM-5 (CAPS-5)).

**Subjects enrolled by Penn Researchers**

0

**Subjects enrolled by Collaborating Researchers**

120

*7.2. Accrual*

Provider-participants: The On-Site PI will present information about the study and participation to all mental health providers who provide psychotherapy at each site. Those who meet the inclusion and exclusion criteria will be invited to participate in the study and provided informed consent. The project coordinator and research assistant at each site will assist with the coordination of recruitment, screening, and informed consent of participants.

Patient-participants: Patients who screen positive for PTSD according to the PCL-5, PCL-C, or whichever screening measure is used as the performance site’s screening tool for PTS, and who are assigned to one of the provider-participants enrolled in the study will be invited to participate in the study and will meet with a member of the research team to review informed consent. Patients who consent to the study will complete a baseline evaluation with a BOA that includes the CAPS, the M.I.N.I, and self-report questionnaires.

*7.3. Key inclusion criteria*

Key inclusion criteria for provider-participants are the following:

- Male and female mental health providers whose job duties include providing psychotherapy to adult patients, ages 18-65, seeking treatment for PTSD.

- 20% of expected patient caseload with trauma related difficulties

- Support from local leadership to ensure that providers are granted the time and resources necessary to participate in study activities, including providing 90-minute once weekly sessions, time off to participate in the training workshop, time to participate in consultation , time to complete study assessments, etc.

Key inclusion criteria for patient-participants are the following:

- Male and female patients aged 18-65 who are seeking treatment from one of the mental health providers participating in this study.

- Clinically significant PTSD symptoms, defined as a severity score of 25 or greater on the Clinician-Administered PTSD Scale for DSM-5 (CAPS-5).

*7.4. Key exclusion criteria*

Key exclusion criteria for provider- participants are the following:

- Definite plans to terminate their position or relocate from the Army base at some point during the 1 year following training.

- Extensive previous training in Prolonged Exposure (PE), defined as participation in a 4-day PE training workshop at any point prior to the start of the study, and self-reported use of PE (including both imaginal and in vivo exposure techniques) to treat 4 or more patients with PTSD in the past year.

Key exclusion criteria for patient participants:

- Current bipolar disorder I or psychotic disorder (as determined by the MINI).

- Evidence of a moderate or severe traumatic brain injury (as determined by the inability to comprehend the baseline screening questionnaires).

- Current suicidal ideation severe enough to warrant immediate attention (as determined by the Beck Scale for Suicidal Ideation).

*7.5. Vulnerable Populations*

Children Form

Pregnant women (if the study procedures may affect the condition of the pregnant woman or fetus) Form

Fetuses and/or Neonates Form

Prisoners Form

Other

x None of the above populations are included in the research study

*7.6. Populations vulnerable to undue influence or coercion*

Study staff will emphasize to participating providers that the decision to implement PE in regular treatment of PTSD is voluntary and will not affect their status in the military or as a civilian or any benefits that they typically receive. Patients of participating providers will be informed that they can withdraw from the study at any time with no consequences and will be at no risk of losing their right to medical or psychological care with the providers.

*7.7. Subject recruitment*

Provider-participants: The On-Site PI will present information about the study to all mental health providers who provide psychotherapy. Mental health providers who meet the inclusion and exclusion criteria will be invited to participate in the study and provided informed consent. The project coordinator and research assistant at each site will assist with the coordination of recruitment, screening, and informed consent of provider participants.

Patient-participants: Patients seeking mental health services complete a packet of self-report measures via paper copy or the Behavioral Health Data Platform (BHDP) as part of the routine clinic intake process. In particular, patients will complete a self-report measure of PTSD symptom severity (the PCL-C, PCL-5, or whatever the performance site’s current screening tool for PTS is). Participating providers will be asked to notify patients who meet the screening criteria for PTS symptoms according to the screening measure administered of the option to participate in the study. Under a partial HIPAA waiver for screening, research staff will review the screening scores and alert participating providers of any patients they are scheduled to treat who meet the screening criteria). Research staff will track the names of referred patients that have been sent to providers using a tracking spreadsheet, which will be destroyed once recruitment goals are met. Provider-participants will inform the potential patient-participant that their participation is voluntary and will not affect their mental health care in any way. If the patient expresses interest in the study, the provider will sign the patient up for a meeting with the Behavioral Outcomes Assessor (BOA) via the AHLTA system when the patient checks out of the provider appointment. During the initial meeting with the BOA, the BOA will discuss the study details with the patient and consent the patient if he/she chooses to participate. Patients consenting will complete an intake assessment with the study Behavioral Outcomes Assessor (BOA).

**Subject compensation***

*Will subjects be financially compensated for their participation?*

No

*If there is subject compensation, provide the schedule for compensation per study visit or session and total amount for entire participation, either as text or separate document.*

Subjects will not be financially compensated for their participation.

**8. Study Procedures**

*8.1. Procedures*

This is a randomized clinical trial comparing two methods of training in Prolonged Exposure (PE) treatment. Consented mental health providers at three medium-to-large Continental United States (CONUS) Army installations will be randomly assigned to either implement Standard PE training or Extended PE training. Mental health providers at three military installations will be invited to participate in a 4-day PE workshop which will be conducted at the military site by PE experts from the University of Pennsylvania’s Center for the Treatment and Study of Anxiety. The PE expert conducting the workshop were trained by and work closely with [name], the developer of PE and one of the world’s leading experts in PTSD and PTSD treatment. As part of the PE workshop, the provider will receive training materials and treatment manuals. Following enrollment in the study, provider-participants will also receive an email/letter from the PI, [name], thanking them for their study participation. Following the 4-day workshop, participants randomized to the Extended PE training will receive weekly case consultation from PE experts on two PE training cases including the review of video-tapes made of their two supervised cases. Patient consent to these video-recordings of clinical care will be accomplished by each sites local form for recording of patient care. These training case patients are not considered study participants. Provider will obtain consent from their patients to video-record using a separate clinical consent document. The video-recordings of the training cases will be copied onto DVD at the individual performance sites, labeled with the providers study number, and mailed directly to the University of Pennsylvania Center for the Treatment of Anxiety for review as part of case consultation teleconferences using an express service (e.g., FedEx) and tracked for receipt.

Participants randomized to the Standard PE training group will not receive any additional consultation following the workshop. In addition to mental health providers, patients seeking treatment from participating providers will be recruited and consented to examine their symptoms of PTSD and related problems during treatment. Providers will not be required to use PE therapy to treat their patients with PTSD; rather it will be an option for treatment. A diagnostic feedback form will be given to the provider by the BOA within 24-hours (with more time allotted as needed on a case-by-case basis) of completing both the first and second assessments and will contain a summary of the assessment data. This assessment data may be used by the provider, as he or she deems appropriate, for ongoing treatment decisions. Clinical care of patients enrolled in this study will not be video-taped. Choice of treatment modality will be one of the outcome measures; data on techniques used in treatment will be collected from study providers after every session with a study patient via the Procedures Used in Treatment Checklist. The Checklist will also be used by providers to record their study patients’ self-reported PTS and depression scores, which the providers will acquire from their AHLTA (medical record) session notes on a biweekly basis.

*8.2. Analysis Plan*

The first set of Objectives concern therapist behaviors, specifically hypothesizing that Extended Training will result in a greater proportion of PTSD patients treated with PE, use of PE with more complex patients (e.g. comorbidities). The analyses will be done using mixed effects regression models with repeated measures, incorporating as covariates baseline values on the outcome measures when available and confounded ancillary variables as needed. Planned between and within-group contrasts will be done at each assessment by t-test. The measures to address the first two objectives will be derived from self-report scales completed after consultation. When feasible, summary measures will be derived by summing items bearing on the same issue. For example, the Implementation Survey includes a 25-item section listing comorbid conditions and complicating factors. The fidelity analysis will be based on ratings by IEs of recorded sessions.

The second set of Objectives concerns changes in therapist attitudes. The analysis model will be mixed effects regression as above, with intervention arm the primary independent variable and repeated measures at post-consultation and at two and three years. The dependent measures will be summary scores derived from the Implementation Surveys, using sums of relevant items as appropriate to operationalize therapist self-efficacy, satisfaction and expectations for change. We anticipate that changes in therapist attitudes may appear very quickly in the training process, influenced by expectations about consultation and supervision at the earliest stages and experience of training as it is received.

The third set of Objectives concern changes in patient outcomes, specifically PTSD symptom severity, other symptoms, dropout, and satisfaction with treatment. The analysis design for continuous measures based on self-report scales is simple analysis of (co)variance on post-treatment outcomes (or equivalently, change), comparing intervention arms using pre-treatment measures as covariates. If dropout data are available at the individual patient level, simple chi-square, logistic regression or generalized mixed effects models will be used to compare interventions. For all patient level outcomes, mixed models may be needed because patients are nested within therapists. Preliminary analyses will explore the need to include therapist as a random design effect to account for possible clustering effects (Crits-Christoph & Mintz, 1991). For the therapist level outcomes, the impact of baseline patient (or therapist) characteristics that are confounded with intervention condition will be evaluated using analysis of covariance.

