5.2.2. Primary outcome variable(s)

The first set of Objectives concern provider behaviors, specifically hypothesizing that Extended Training will result in a greater proportion of PTSD patients treated with PE, use of PE with more complex patients (i.e., those with greater severity, complicating factors, and/or comorbidities), and better adherence to the PE protocol in those cases treated with PE. The measures to address this objective will be derived from self-report scales completed after consultation. When feasible, summary measures will be derived by summing items bearing on the same issue. For example, the Implementation Survey includes a 25-item section listing comorbid conditions and complicating factors. The fidelity analysis will be based on ratings by IEs of recorded sessions. Another set of Objectives concerns changes in provider attitudes. The outcome measures will be summary scores derived from the Implementation Surveys, using sums of relevant items as appropriate to operationalize provider self-efficacy, satisfaction and expectations for change.

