There is no plan to destroy research documents or data files. Participant identifiers and PHI for both mental health providers and patients seeking treatment will be destroyed upon closure of the study with the IRBs. Informed consent documents will be stored securely for three years following completion of the research; HIPAA authorizations will be stored for six years IAW Federal regulations. Video-recordings of training cases will be copied onto DVD at the individual performance sites, labeled with the providers study number, and mailed directly to the University of Pennsylvania Center for the Treatment of Anxiety for review as part of case consultation teleconferences using an express service (e.g., FedEx) and tracked for receipt. Following review with the participant provider, the tapes will be destroyed by the Center for the Treatment of Anxiety staff.

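### The rated-fidelity comparison listed among the primary outcomes has no described recordings in the Standard arm, so it cannot be estimated as written

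*Protocol*

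**What the plan says.** Section 5.2.2 of the protocol, which lists the primary outcome variables, sets out three provider-behaviour hypotheses in favour of Extended training. The third is "better adherence to the PE protocol in those cases treated with PE". The same section assigns the data source, and section 8.2 (Analysis Plan) repeats it: "The fidelity analysis will be based on ratings by IEs of recorded sessions".

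Section 8.1 (Procedures) says what is recorded. For patients in the study: "Clinical care of patients enrolled in this study will not be video-taped". For Extended-arm providers, consultation covers two training cases, "including the review of video-tapes made of their two supervised cases". Of the patients in those cases it says: "These training case patients are not considered study participants". For the other arm: "Participants randomized to the Standard PE training group will not receive any additional consultation following the workshop".

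Sections 8.1 and 9.1 give the purpose of the tapes as "for review as part of case consultation teleconferences". Section 9.1 adds that, once they have been reviewed with the provider, "the tapes will be destroyed by the Center for the Treatment of Anxiety staff".

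**The concern.** The adherence hypothesis is comparative: it predicts that Extended providers will follow the PE protocol better than Standard providers. Testing it on rated recordings needs recordings from both arms. The procedures describe recordings from one arm only, and those come from patients who are not in the trial and whose therapist is under expert supervision at the time.

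An outcome listed as primary would then either go unreported or be replaced by another measure chosen after the data are in. Alternatively, ratings from the Extended training cases could be presented as if they answered the hypothesis, when they only describe supervised cases in one arm.

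**Working it through.** No formula in the protocol can be reproduced here. The question is whether the data exist, so the check sets the statements side by side and counts the recordings.

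**Inputs**

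| Item | Where | Content |
|---|---|---|
| Hypothesis | 5.2.2 | Better adherence under Extended, in cases treated with PE |
| Data source | 5.2.2 and 8.2 | Rated recordings |
| Video of study patients | 8.1 | None, either arm |
| Video of training cases, Extended | 8.1 | Two supervised cases per provider |
| Video of training cases, Standard | 8.1 | None described; no consultation in this arm |
| Training-case patients | 8.1 | Not study participants |
| Use of tapes | 8.1 and 9.1 | Consultation review, then destruction; no independent rating step described |
| Providers | Protocol Description; 2.4 | 120 in total; about 100 per condition |

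**Count of ratable cases**

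- Study patients: 0 in Standard and 0 in Extended.
- Training cases, Standard: 0.
- Training cases, Extended: up to 2 × number of Extended providers.
  - With 120 providers and an assumed 1:1 split, 120 / 2 = 60 providers, and 2 × 60 = 120 cases.
  - With about 100 providers per condition, 2 × 100 = 200 cases.

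The protocol gives both provider totals, so both are shown. The choice does not matter to the conclusion, because the Standard count is 0 in either case.

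**Consequence for the estimate**

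The target is the mean rated fidelity in Extended minus the mean in Standard. With no rated case in Standard, the second mean does not exist. Its variance term, σ² / n with n = 0, is undefined. More Extended cases, covariates or a random provider effect do not change this, so the mixed models of section 8.2 have nothing to contrast.

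**What is collected in both arms**

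The only session-level treatment data described without restriction to one arm come from the Procedures Used in Treatment Checklist, which providers fill in after each session with a study patient (8.1). Section 2.1 describes it as a 4-item form on the techniques used. It is reported by the provider and is not a rating of recordings.

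**The case against.** Five points can be made for the plan.

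- **A separate analysis plan may settle it.** It could define scales and models, but it cannot analyse recordings that the protocol says will not be made. The data source is fixed in the protocol, so this does not stand.
- **Audio is not excluded.** Section 8.1 rules out video only, and that stands as a matter of wording. No audio recording is described, however, and the session tapes mentioned in section 6.5 belong to a general account of the coordinating centre's facilities.
- **Self-report covers the objective.** Section 5.2.2 does say that measures for this set come from self-report scales, and the Checklist is used in both arms. A reader might therefore infer too much from a statement that the adherence outcome has no control-arm data of any kind. What has none is the rated-fidelity analysis, to which 5.2.2 gives its own source.
- **The tapes could be rated before they are destroyed.** This stands. A reader might infer that destruction is what makes the comparison impossible, but it follows review with the provider, so earlier rating is feasible. The obstacle is the empty Standard arm. Nor does the text describe live coaching: it describes supervised cases whose tapes are reviewed later.
- **Adherence is not central.** It is absent from the overall hypotheses in 5.2.1, from the major outcomes named in 5.1 and 6.1, and from the hypotheses that open 8.2. The adherence clause and the fidelity sentence may be leftover text. That limits the damage, but 5.2.2 still lists adherence under primary outcomes and 8.2 still announces the analysis.

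**Conclusion.** The contradiction is real and needs correction. As described, the procedures give 0 ratable cases in Standard and up to 120 (60 Extended providers) or up to 200 (100 Extended providers) training cases in Extended, all in patients outside the study. The stated between-arm comparison of rated fidelity cannot be estimated at any sample size.

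This rests on two readings: that no recording exists beyond those the protocol describes, and, for the figure of 120 only, that allocation is 1:1.

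The finding does not reach further. A reader might infer that the trial's primary question fails, but the analyses of PE use, provider attitudes and patient outcomes do not depend on recordings.

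**What to change.** Reconcile sections 5.2.2, 8.1 and 8.2:

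1. Remove independently rated fidelity as a between-arm primary outcome from 5.2.2 and 8.2.
2. If training-case tapes are rated before destruction, report the ratings only as a description of the Extended arm.
3. If an adherence comparison is kept, make it secondary and define it as provider-reported delivery of PE components, taken from the Procedures Used in Treatment Checklist.

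Three limits should be written beside any Checklist measure:

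- The text shown does not give the content of the four items. It must be confirmed that they capture imaginal and in vivo exposure.
- The form records whether components were delivered, not how well.
- Neither analysis set is clean. Over all study patients, the measure overlaps with the PE-use outcome, because a patient not treated with PE would score near zero. Restricted to PE-treated cases, it compares subsets formed after randomisation. PE is optional and Extended training is expected to raise its use and widen it to more complex patients, so those subsets may differ by arm.

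The cost is a wording change and, if item 3 is adopted, one derived variable from a form already in use, subject to the item check. The trial gives up an independently rated fidelity claim that its described procedures could not support. Keeping such a claim would require comparable recording and rating in both arms, which section 8.1 does not provide for.

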**2. Study Instruments**

*2.1. Provider Measures*

Provider Demographics & Background Survey: The Provider Demographics Form assesses standard demographics (ethnicity, gender, age, etc.) and professional information (e.g., military rank, type of schooling, etc.). It also includes items designed to assess providers training, theoretical orientation and experience providing evidence-based treatments, including their knowledge of PE, experience with PE, and attitudes towards PE. This measure will be completed by providers in both conditions.

Provider Measure of Attitudes: This is a 59-item measure of current treatment practices (7 items), beliefs about the effectiveness of PE (1 item), self-confidence in delivering PE (8 items), and perceptions about patient factors that would influence providers decision to use PE (22 items). In addition, this measure includes an embedded, modified version of the 21-item Therapist Beliefs about Exposure Scale (TBES; Deacon et al, 2013). All TBES items were modified to refer to PE specifically, rather than exposure therapy which is a more general term. The TBES has strong psychometric properties including excellent internal consistency ( = .90-.96), high test-retest reliability (r = .89; Deacon et al., 2013). The Provider Measure of Attitudes will be completed by providers in both conditions prior to attending the PE training workshop, after attending the PE training workshop, and at regular 3-month intervals over the course of 18 months following the completion of training (i.e. for providers in the standard condition, after the completion of the training workshop; for providers in the extended condition, after the completion of two supervised PE training cases).

Procedures Used in Treatment Checklist: This 4-item form is meant to collect data on what treatment techniques providers used during their sessions with study patients. Providers will also use the form to record patients’ biweekly PCL and PHQ-9 scores.

*2.2. Patient Measures*

Patient Demographics: The Patient Demographics Form assesses standard demographics (ethnicity, gender, age, etc.).

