**2.3. Group Modifications**

There will not be any modifications to any study instruments for different groups. However, only the Extended PE training condition will complete the Provider Post-Consultation Measure of Attitudes because they will be the only group that receives consultation.

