**2.5. Administration of Surveys and/or Process**

All participants will attend a 4-day workshop in prolonged exposure. All participants will all complete self-report measures at various time points: 1) prior to completing the workshop, 2) after completing the workshop, and 3) at 3-month intervals over the course of the 18 months following the completion of training (for standard providers, following the workshop; for extended providers, following their 2 supervised PE training cases). These self-report measures should take approximately 20-30 minutes to complete. Participants who are randomized to Extended PE training condition will additionally be asked to participate in weekly telephone consultation for two PE training cases, which we expect to last approximately 6 months. Patients of the participating providers who consent will be evaluated at two time points: once before they begin treatment (first assessment) and once after receiving 8-15 sessions of treatment, or after 5 months since the initial assessment, whichever comes first (second assessment). Patients who complete or leave the study before receiving 8 sessions of treatment will be asked to complete a second assessment at the time of termination. The consent and first assessment sessions will take a total of 2 to 2.5 hours. The second assessment will take approximately 1 hour. Patients will also be asked to complete self-report measures every 14 days. These measures can take 10-15 minutes to complete.

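### Section 8.2 models provider attitudes at three time points, none scheduled in both arms, and leaves out the six quarterly waves that are collected

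*Protocol*

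**What the plan says.** **Analysis.** In Section 8.2 the attitude analysis is a mixed-effects regression with training arm as the main predictor and "repeated measures at post-consultation and at two and three years". Section 5.2.2 lists attitudes under the primary outcome variables, and Section 5.2.1 makes them one of three hypotheses comparing the arms.

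**Collection.** Section 2.1 has the Provider Measure of Attitudes completed before the workshop, after it, and "at regular 3-month intervals over the course of 18 months following the completion of training". Section 2.5 repeats this for the provider self-report measures as a whole: "at 3-month intervals over the course of the 18 months following the completion of training". The end of training differs by arm. It is "for providers in the standard condition, after the completion of the training workshop", but for Extended providers it is the completion of two supervised cases, which Section 2.5 expects to take about six months.

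**Post-consultation.** Section 2.3 states that "only the Extended PE training condition will complete the Provider Post-Consultation Measure of Attitudes".

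**Calendar.** Section 6.2 says "The study is expected to start in May 2014 and end in May 2017", with recruitment and data collection mostly in years 2, 3 and 4 and analysis in year 4. Section 6.6 refers to four years of funding.

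**Per-assessment contrasts.** Under the provider-behavior objectives, Section 8.2 adds: "Planned between and within-group contrasts will be done at each assessment by t-test".

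**The concern.** The analysis section and the collection sections describe different sets of visits. An arm comparison needs a measurement in both arms at the time point where it is made. If the named time points have none, the stated analysis of a primary outcome cannot be carried out as written. Someone will then have to choose other visits, possibly after seeing the data. That choice matters because the two arms start their quarterly follow-up about six months apart: comparing visits by wave number and comparing them by time since the workshop are different questions and may give different answers. The protocol does not say which is meant.

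**Working it through.** The protocol gives no significance level, power or sample-size calculation for attitudes, so there is no stated figure to reproduce. The check sets the visits side by side.

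**Inputs.** Six follow-up visits at three-month spacing to 18 months after training (Sections 2.1 and 2.5). Training ends at the workshop for Standard, and about 6 months later for Extended (Section 2.5).

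**Visit times in months from the workshop**, for k = 1 to 6:

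- Standard: 3k = 3, 6, 9, 12, 15, 18.
- Extended: 6 + 3k = 9, 12, 15, 18, 21, 24 (approximate, since the 6 months is an expectation).
- Shared: 9, 12, 15, 18. The pre- and post-workshop measures are also common to both arms.
- No counterpart in the other arm: Standard's months 3 and 6, Extended's months 21 and 24.

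Counted instead from each arm's own end of training, both arms have months 3, 6, 9, 12, 15 and 18, with Extended about 6 months later in calendar time at every wave.

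**The three named time points against that schedule:**

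| Time point in Section 8.2 | Standard | Extended | Both arms? |
|---|---|---|---|
| Post-consultation | no consultation, measure not completed | completed | no |
| Two years from workshop | last visit at month 18 | about month 24 | no |
| Two years from end of training | last visit at month 18 | last visit at month 18 | no |
| Three years, either origin | none | none | no |

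The result is 0 of 3.

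**Calendar.** May 2014 to May 2017 is 36 months. A provider trained at the start of year 2 (month 12) would reach three years at 12 + 36 = 48 months. That is past the stated end and at the very end of a four-year funding period in which year 4 is also for analysis. The three-versus-four-year discrepancy therefore does not create room for a three-year visit.

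**Instrument name.** Section 8.2 takes the attitude scores from the Implementation Surveys, a name not listed in Section 2.1. The schedule in Section 2.5 covers provider self-report measures in general, so the result does not depend on which form is meant.

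**Conditional size of the per-assessment tests.** This assumes a two-sided 5% level, six visits, one outcome, and that any single significant visit would count as success. None of these is a rule in the protocol. With independent visits, 1 − 0.95^6 = 26.5%. With equally correlated test statistics (simulation, 400,000 draws):

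| Correlation between visits (assumed) | Chance of at least one false positive |
|---|---|
| 0.3 | 24.1% |
| 0.5 | 20.7% |
| 0.7 | 16.4% |
| 0.8 | 14.0% |
| 0.9 | 10.8% |

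The only stability figure in the protocol is the test-retest r of .89 for the beliefs-about-exposure scale (Section 2.1, interval not given), which would point to the lower end.

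**The case against.** **The model is not beyond use.** A reader might infer that the attitude comparison cannot be run at all. The documents do not support that. The mixed model can be fitted to the quarterly waves without new data, and only its list of time points is wrong. Nor is the two-year point wholly absent, since the last Extended visit falls about 24 months after the workshop. One could also pair Standard's post-workshop measure with Extended's post-consultation measure, as each marks the end of training. That pairing is about six months apart in time, and Section 8.2 does not state it.

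**The t-tests are not shown to inflate error.** A reader might see the per-assessment t-tests as a fallback that discards the baseline value and produces many false positives. The text calls them planned contrasts and puts them beside a mixed model that uses baseline values as covariates. Contrasts from such a model are commonly tested with t statistics. The sentence stands under provider behaviors, and its extension to attitudes through the later cross-reference is inference. No level or success rule is stated, and multiplicity may be handled in a statistical analysis plan that is not shown.

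**Nor can the rate be multiplied across outcomes.** A reader might count six outcomes at six waves and arrive at a much higher figure. Section 8.2 bases fidelity on ratings of recorded sessions, not on the quarterly surveys, and three of the six would be attitude scores to which the t-test sentence is not clearly applied.

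**What stands.** None of this repairs the visit list. An analysis plan could cure it only by departing from the protocol's explicit text.

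**Conclusion.** The contradiction is real and must be reconciled. None of the three time points named for the attitude model has a scheduled measurement in both arms, and the six quarterly waves are not in that model. The post-consultation and three-year results follow directly from the text. The two-year result holds under either time origin. The month-by-month overlap rests on consultation taking about six months, as Section 2.5 expects, and will shift for individual providers.

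Multiplicity is a secondary and conditional remark: about 11% to 26% for one outcome over six visits, depending on the assumed correlation, and only if any one significant visit counted as success. It is not shown to be a fault of this plan.

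**What to change.** In Section 8.2, replace the three time points with visits collected in both arms. Keep the same mixed model, adjusted for the pre-workshop score, and state the time origin as one of these:

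- **Time since the workshop.** Shared visits are post-workshop and about months 9, 12, 15 and 18. Standard's months 3 and 6 and Extended's months 21 and 24 then have no counterpart in the other arm.
- **Time since end of training.** Shared visits are months 3 to 18 in steps of three. All six waves are used, but Extended is measured about six months later in calendar time, and the protocol should say so.

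Name the arm contrast that answers the attitude hypothesis, estimated from the model; month 12 after the workshop is one example that both arms reach. Describe per-assessment contrasts as supportive. If six per-visit tests were instead meant to decide the question, a Bonferroni level would be 0.05/6 = 0.0083 each.

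The cost is analysis wording only. Neither option needs a new visit, and the place of attitudes among the primary outcomes need not change.
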